# Oral fosfomycin versus ciprofloxacin in women with *E.coli* febrile urinary tract infection, a double-blind placebo-controlled randomized controlled non-inferiority trial (FORECAST)

**DOI:** 10.1186/s12879-018-3562-2

**Published:** 2018-12-05

**Keywords:** Fosfomycin-trometamol, Urinary tract infection, *Scherichia coli*, Antibiotic treatment, Randomized clinical trial

## Abstract

**Background:**

Febrile Urinary Tract Infection (FUTI) is frequently treated initially with intravenous antibiotics, followed by oral antibiotics guided by clinical response and bacterial susceptibility patterns. Due to increasing infection rates with multiresistant Enterobacteriaceae, antibiotic options for stepdown treatment decline and patients more frequently require continued intravenous antibiotic treatment for FUTI. Fosfomycin is an antibiotic with high bactericidal activity against *Escherichia coli* and current resistance rates are low in most countries. Oral Fosfomycin-Trometamol 3000 mg (FT) reaches appropriate antibiotic concentrations in urine and blood and is considered safe. As such, it is a potential alternative for stepdown treatment.

**Methods:**

The FORECAST study (Fosfomycin Randomized controlled trial for *E.coli* urinary tract infections as Alternative Stepdown Treatment) is a randomized, double-blind, double-dummy, non-inferiority trial in which 240 patients will be randomly allocated to a stepdown treatment with FT or ciprofloxacin (standard of care) for FUTI, caused by *Escherichia coli* with in vitro susceptibility to both antibiotics*.* The study population consists of consenting female patients (≥18 years) with community acquired *E. coli* FUTI. After intravenous antibiotic treatment during at least 48 (but less than 120) hours, and if eligibility criteria for iv-oral switch are met, patients receive either FT (3 g every 24 h) or ciprofloxacin (500 mg every 12 h) for a total antibiotic duration of 10 days. The primary endpoint is clinical cure (resolution of symptoms) 6–10 days post-treatment. Secondary endpoints are microbiological cure 6–10 days post-treatment, clinical cure, mortality, ICU admittance, relapse, reinfection, readmission, additional antibiotic use for UTI, early study discontinuation, adverse events, days of hospitalization and days of absenteeism within 30–35 days post-treatment. The sample size is based on achieving non-inferiority on the primary endpoint, applying a non-inferiority margin of 10%, a two-sided *p*-value of < 0.05 and a power of 80%.

**Discussion:**

The study aims to demonstrate non-inferiority of oral fosfomycin, compared to oral ciprofloxacin, in the stepdown treatment of *E. coli* FUTI.

**Trial registration:**

Registered at the Nederlands trial register (Dutch trial register) on 4-10-2017. Trial registration number: NTR6449. Secondary ID (national authority): NL60186.041.17.

## Background

Urinary Tract Infections (UTI) are the most common bacterial infections requiring antibiotic treatment in the western world [1]. Complicated urinary tract infections (cUTI) are defined upon the presence of systemic symptoms or upon the susceptibility of the host for a complicated course [2]. Systemic symptoms are often fever, febrile UTI (FUTI), or other symptoms, reflecting the presence of tissue infection such as pyelonephritis, prostatitis or the urosepsis syndrome [2]. Guidelines recommend to treat FUTI with a 7–14 day course of antibiotics [2, 3] and in the majority of cases empiric intravenous antibiotics will be followed by oral stepdown therapy. The choice of stepdown treatment should be targeted to the susceptibility pattern of the causal uropathogen. Unfortunately, antibiotic options for stepdown treatment are becoming limited as the result of increasing antibiotic resistance [2].

*Escherichia coli* (*E.coli*) is the causative organism in around 70–75% of FUTI [4, 5]. In 2017, resistance rates of *E. coli* isolates of patients admitted to Dutch hospitals were 14% for ciprofloxacin (CPX), 23% for trimethoprim-sulfamethoxazole and 36% for amoxicillin-clavulanic acid with higher resistance rates in patients from urology departments [6]. Though this leaves fluoroquinolones still as one of the oral antibiotics to treat FUTI, one of the goals of antibiotic stewardship is to reduce fluoroquinolone use because of its selective properties for antibiotic resistance [2]. In the Netherlands, about 2–5% of patients hospitalized for community-acquired FUTI cannot be treated with oral antibiotics due to antibiotic resistance of the causal uropathogen [7]. This implies the need of prolonged intravenous antibiotic treatment, prolonged hospitalization, increased healthcare costs and higher risks of forthcoming complications.

Fosfomycin is an alternative antibiotic treatment for the stepdown treatment of FUTI [8, 9]. Fosfomycin is a phosphoenolpyruvate analogue and orally available as Fosfomycin-Trometamol (FT). It has been used extensively for uncomplicated cystitis in women, has a good safety profile [10] and possesses a suitable pharmacokinetic profile in healthy volunteers.

In the FORECAST trial (FOsfomycin Randomized controlled trial for *E.coli* urinary tract infections as Alternative Stepdown Treatment), we will investigate the efficacy of FT when used as stepdown therapy of FUTI in women.

## Methods

The objective of this randomized controlled double-blind, double-dummy, non-inferiority, multicentre, investigator-initiated trial is to determine whether oral FT is non-inferior to oral CPX in the step-down treatment of *E.coli* FUTI in women for achieving clinical cure. The study will be performed in 15 Dutch hospitals; 4 academic centers and 11 large teaching hospitals.

### Participants

#### Inclusion criteria

Competent women (≥18 years), that are hospitalized for the presumed diagnosis FUTI and receive appropriate empirical intravenous antibiotics for ≥48 - ≤120 h, who are judged to be eligible for an intravenous-oral switch by the attending physician, according to the Dutch guideline, that recommends to switch therapy until the patient has been afebrile for 24–48 h and symptoms have improved [2]. Urine (≥10^4^ CFU/ml) or blood culture must reveal *E.coli*, susceptible to both CPX and fosfomycin. A patient is not eligible if non-E.*coli*-type Enterobacteriaceae are present in urine culture (≥10^3^ CFU/ml) or blood culture.

FUTI is defined as UTI with at least one forthcoming systemic symptom or sign and one local symptom at presentation. Local symptoms are dysuria, urinary urgency, urinary frequency, suprapubic/pelvic discomfort, macroscopic hematuria, new urinary incontinence or worsening of pre-existing incontinence, lower abdominal pain, low back pain, flank pain, costo-vertebral angle pain or tenderness on physical examination. Systemic symptoms or signs are fever (≥38.0 C ͦ) or low temperature (< 36 C ͦ), rigors, delirium, hemodynamic instability as a result of sepsis requiring intravenous fluids or an increase in CRP (≥30 mg/L) or leucocytes (≥12*10^9^/L). Local symptoms are not required in case the urine and blood culture yield are positive for a phenotypically identical matched E.coli and UTI is the presumed source of infection according to the treating physician.

Adequate empirical intravenous treatment may consist of amoxicillin+/−clavulanic acid, 2nd or 3rd generation cephalosporin, aminoglycoside, carbapenem, fluoroquinolones, trimethoprim-sulfamethoxazole or a combination and in vitro susceptibility of the causative *E.coli* to at least one of the used agents.

#### Exclusion criteria

Pregnancy or breastfeeding, glomerular filtration rate below 30 ml/min/1,73 m3 or renal replacement therapy, concomitant systemic antibacterial treatment, ascertained or presumptive hypersensitivity to (compounds of) the study products, participation in any trial with an investigational product involved in the 30 days before the screening visit, specific patient groups: patients with renal transplant, polycystic kidney disease, neutropenia (< 500 /μl), paraplegia, suspicion/presence of renal abscess, suspicion of septic metastatic foci/endocarditis, urostomy, ileal loops, long-term urinary catheter (placed ≥24 h before admission), e.g., double-J catheter, nephrostomy catheter, suprapubic catheter, specific contra-indications for CPX or fosfomycin: concurrent use of tizanidin, clozapin or theophylline, a history of tendon disease/disorder related to quinolone treatment, patients with known risk factors for prolongation of the QT interval, glucose-6-phosphate dehydrogenase deficiency, inadequate understanding of the study risks or its requirements or unwilling to plan a follow-up visit and every other laboratory result, clinical condition, disease or treatment that, in investigator’s opinion, make the subject non suitable for the study. Patients with partial obstruction of the urinary tract, ureteral stones or intermittent catheterization will not be excluded.

### Setting

Potential subjects for inclusion will be identified through daily screening for *E. coli* in urine and blood cultures in the clinical microbiology laboratories of participating centres. The study investigator will assess potential subjects for eligibility with consultation of the attending physician. After identification, eligible patients will be informed and, after obtaining consent, will be randomized.

### Randomization

The data manager of the University Medical Centre Utrecht constructed a randomization list, that connects the unique medication code with the active substance (1:1). Only the data manager and the pharmacist on duty, responsible for the deblinding process in case of emergency, have access to the randomization code. Constrained randomization will take place with permuted blocks, that contain a pre-specified number of treatment assignments in a random order. As we expect to include more than 200 participants in a two-arm trial, the probability of a significant imbalance is negligible [11]. To prevent imbalances between both study arms stratification will be performed per study centre, as each study centre handles their own local guideline for the empirical treatment of FUTI.

### Treatment

Participants will be randomized for an intravenous-oral antibiotic switch to either FT 3000 mg every 24 h or CPX 500 mg every 12 h [1]. CPX is chosen for the control group, because most evidence exists for CPX as an oral treatment of FUTI [12, 13]. A double-dummy design is chosen as it is impossible to equalize fosfomycin granules to any form of CPX. An identical placebo will be used for both active substances. All medicines will be manufactured according to Good Manufacturing Principles by the pharmaceutical company Basic Pharma BV, the Netherlands. The duration of total antibiotic therapy is 10 days for all participants, of which 2–5 days empirical intravenous antibiotics and the remaining 5–8 days stepdown therapy with FT or CPX.

FT will be dosed 3 g every 24 h, which is based on a review of the scientific data and expert opinion on the treatment of FUTI and the pharmacokinetics of FT that was available at the moment the study was designed (May 2017). The use of FT every 24 h for more than a single dose was tolerated well in retrospective studies and according to personal off-label use [14]. We do not expect negative effects of accumulation as fosfomycin is registered for intravenous use in dosages as high as 24 g per 24 h [15]. A medication diary needs to be filled by the participant in order to improve medication adherence. All patients receive oral and written information on the trial, including possible risks of participating. Additionally, patients receive a medication folder with instructions for use, contra-indications, interactions and adverse events of both FT and CPX (probable, possible and seldom adverse events). For questions or concerns, participants could contact the local or principle investigator or an independent expert physician.

### Data collection

In each hospital, authorized and qualified clinical investigators and research nurses will obtain informed consent for participation. Demographic, clinical and microbiological data will be collected and stored for at least 15 years. Data will be collected from questionnaires and supplemented with data from the electronic medical record, see Table 1.

**Table 1 Tab1:** Enrolment, interventions and assessments in the FORECAST study

	Patient identification	Before randomization	Study treatment (5–8 days)	6–10 days post-end of treatment	30–35 days post-end of treatment
Enrolment:					
Screening for eligibility	x				
Entry criteria		x			
Informed consent		x			
Interventions:					
Venapunction^a^		x			
Urine/blood culture	x			x (urine)	
Study treatment			x		
Assessments:					
Electronic patient file		x		x	x
Patient questionnaire		x		x	x
Hand in study diary and residual study medicines				x	

^a^in case of doubt about the following exclusion criteria: pregnancy, neutropenia or renal insufficiency

All participating microbiological and clinical chemistry laboratories are accredited by the Dutch foundation for the promotion of the quality and the accreditation of laboratories in health care (ISO). Susceptibility to fosfomycin and CPX is tested using validated local susceptibility methods, following the European Committee on Antimicrobial Susceptibility (EUCAST) recommendations. The clinical (*E. coli*) isolates will be stored for additional susceptibility measurements, i.e. agar dilution for fosfomycin susceptibility, and molecular analysis.

The primary and secondary endpoints will be collected 6–10 days post-end-of-treatment during a visit and 30–35 days post-end-of-treatment by telephone. Data will be entered into the Case Report Form (CRF) pseudo-anonymously in each participating centre using an unique participant code. The data will be processed by the data management program ‘ResearchOnline’. All steps of the data process will be stored to be able to check validity and plausibility.

### Endpoints

The primary endpoint is clinical cure (resolution of symptoms) 6–10 days post end-of-treatment. Definitions and criteria of primary and secondary endpoints are described in Table 2.

**Table 2 Tab2:** Endpoints, provided with definitions and a time frame

Endpoint	Definition	Time frame
Clinical cure	Alive with reduction of all initial local and systemic FUTI related symptoms and without additional systemic antibiotic therapy for UTI (except antibiotic prophylaxis)	6–10 days post-end of-treatment (PET) + 30–35 days PET
Microbiological cure	Negative urine culture for E.coli (< 10^3^ CFU/ml), phenotypically identifiable to the initial culture (assessment by microbiologist) ^a^	6–10 days PET
Acquired resistance	Resistance to ciprofloxacin, fosfomycin or new ESBL-producing bacteria in phenotypically identical strain	6–10 days PET
Mortality	-Mortality for any reason	Within 30–35 days PET
	-Mortality related to UTI or study medicines	
ICU admission	-ICU admission for any reason	Within 30–35 days PET
	-ICU admission related to UTI or study medicines	
Readmission	-Readmission for any reason	Within 30–35 days PET
	-Readmission related to UTI or study medicines	
Relapse	Development of new symptoms of UTI after previous clinical and microbiological cure with a phenotypically identical strain as isolated during the initial blood or urine (≥10^3^) cultures.	Within 30–35 days PET
Reinfection	Same definition as relapse, but with phenotypically different strains isolated in cultures (urine, ≥10^3^)	Within 30–35 days PET
Additional antibiotic use	Additional systemic antibiotic therapy for UTI (except antibiotic prophylaxis)	Within 30–35 days PET
Length of hospital stay	-Total days of hospital stay	Within 30–35 days PET
	-Total days of ICU stay	
Days of absenteeism	Converted to full work days:	Within 30–35 PET
	-Paid work	
	-Voluntary work	
Adverse events	Possible or probable related to study protocol	Within 30–35 days PET
Early study medicine discontinuation	Early study medicine discontinuation:	–
	-because of intolerance/adverse events	
	-because of clinical failure	
	-because of resolution of symptoms	

^a^Other strains in urine culture will be reported, but do not fall within this definition

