### Statistical analysis

#### Sample size calculation

We determined the sample size based on an assumed cure rate of 92.5% for both groups and a margin of inferiority of 10%, consistent with assumptions in similar UTI trials [5, 12, 13, 16]. Assuming that a difference of 10.0 percentage points or less is irrelevant and with the two-sided alpha set at 0.05, the sample size needed in the two groups is 109. The study has a 80% power to reject the null hypothesis that the clinical cure rate for the study arm (FT) is 10% lower than the cure rate for the standard of care (CPX). Equivalently, the likelihood is 80% that the two-sided 95.0% confidence interval for the difference in clinical cure rates will exclude a 10% difference in favour of standard care. In order to evaluate 109 patients in both treatment arms, taking into account 10% of lost participants for various reasons, 240 subjects will be enrolled in total.

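### The primary endpoint is resolution of symptoms in the text but only reduction, with no threshold, in the governing Table 2; the looser wording dilutes the comparison towards non-inferiority.

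*Protocol article*

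**What the plan says.** The abstract of the protocol article states: "The primary endpoint is clinical cure (resolution of symptoms) 6–10 days post-treatment". The Endpoints section repeats it: "The primary endpoint is clinical cure (resolution of symptoms) 6–10 days post end-of-treatment". The next sentence there hands the definition over to the table: "Definitions and criteria of primary and secondary endpoints are described in Table 2".

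The clinical cure row of Table 2 reads: "Alive with reduction of all initial local and systemic FUTI related symptoms and without additional systemic antibiotic therapy for UTI", with an exception for prophylaxis. It does not say how much reduction is enough.

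The Inclusion criteria describe the patient at randomisation. She has had 48 to 120 h of appropriate intravenous antibiotics, and her physician judges her fit for the oral switch under a guideline that asks that she be "afebrile for 24–48 h and symptoms have improved". The qualifying symptoms are dated to admission: "FUTI is defined as UTI with at least one forthcoming systemic symptom or sign and one local symptom at presentation".

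The Sample size calculation uses a single "assumed cure rate of 92.5% for both groups and a margin of inferiority of 10" percentage points. It does not say which wording of cure that rate describes.

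**The concern.** The two wordings classify some patients differently. Take a woman whose flank pain eased on intravenous treatment and then stayed at the same milder level through step-down and up to the visit. Under the text she is a failure; under Table 2 she is a cure. Table 2 itself uses the term resolution elsewhere, in the row on early discontinuation of study medicine, so the document has both words available and they do not mean the same.

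The direction matters. Part of what Table 2 credits as cure is the response to intravenous drugs given to both arms before randomisation. Counting that shared response as success pulls the two cure rates together. With a fixed absolute margin, this makes non-inferiority easier to conclude. The same endpoint also feeds the futility assessment after 100 participants, so the ambiguity reaches the interim advice as well as the final result.

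**Working it through.** **1. The plan's own figure.** Inputs from the Sample size calculation: cure 92.5% in both arms, margin 10 points, two-sided alpha 0.05, power 80%.

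n per arm = (1.96 + 0.8416)² × 2 × 0.925 × 0.075 / 0.10² = 7.849 × 0.13875 / 0.01 = 108.9, so 109. This matches the plan. Adding 10% gives 109 × 1.1 = 119.9, so 120 per arm and 240 in total, also as stated. The arithmetic is sound; the open question is what the 92.5% measures.

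**2. Reference point for reduction.** Table 2 speaks of initial symptoms. The FUTI definition dates symptoms to presentation, and the microbiological cure row uses the same adjective for the first culture. I therefore read the comparison as being with presentation, before intravenous treatment. The switch criterion (no fever, improved symptoms) then overlaps heavily with the Table 2 criterion.

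**3. Effect of the looser wording (assumed rates).** The documents give no resolution rates. Assume true resolution of 85% with ciprofloxacin and 75% with fosfomycin, a deficit exactly at the margin. Let a share f of unresolved patients, equal in both arms, be reduced and so count as cured.

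- Observed rate = p + f(1 − p); observed deficit = 10 × (1 − f) points.
- At f = 0.5: 0.85 + 0.5 × 0.15 = 92.5%, and 0.75 + 0.5 × 0.25 = 87.5%. The deficit is 5 points.
- Standard error = √[(0.925 × 0.075 + 0.875 × 0.125)/109] = 0.0405.
- P(non-inferiority) = Φ[(0.10 − 0.05)/0.0405 − 1.96] = Φ(−0.73) = 23%.

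Exact binomial enumeration with the unpooled 95% interval gives slightly different values from this normal approximation:

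| f | Observed rates | Deficit (points) | P(NI), normal | P(NI), exact |
|---|---|---|---|---|
| 0 | 85% v 75% | 10 | 2.5% | 2.7% |
| 0.25 | 88.75% v 81.25% | 7.5 | 7.5% | 8.1% |
| 0.5 | 92.5% v 87.5% | 5 | 23.4% | 25.2% |
| 0.75 | 96.25% v 93.75% | 2.5 | 72.1% | 72.2% |

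If control resolution is instead set anywhere from 80% to 92.5%, the f = 0.5 result is 21% to 37% (exact).

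**4. Power if resolution is the endpoint (assumed equal rates p, 109 per arm).** Power = Φ[0.10/√(2p(1 − p)/109) − 1.96].

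| p | Power at 109 per arm | n per arm for 80% |
|---|---|---|
| 92.5% | 80% | 109 |
| 90% | 69% | 142 |
| 85% | 54% | 201 |
| 80% | 45% | 252 |

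**The case against.** The strongest reply is that Table 2 remains a demanding composite. Cure is judged 6 to 10 days after treatment ends, not at the switch. It requires survival and no further systemic antibiotic for UTI, so a step-down failure that leads to re-treatment is a failure under either wording. It requires reduction of every initial symptom, whereas the switch guideline asks only that symptoms have improved, so a patient can be randomised without yet meeting Table 2. All of this stands. A reader might infer that the endpoint is already satisfied at baseline and cannot separate an effective from an ineffective drug. The documents do not support that: sensitivity is reduced, not abolished, and even the example above leaves a 5-point difference.

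A reader might also infer that raised CRP or leucocytes must be shown to fall, although Table 1 schedules no blood test at follow-up. That does not hold either. Table 2 refers to symptoms, while the Discussion calls CRP and leucocytes a systemic sign.

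A third reply is that the rates and shares are invented, and that 25% is an error rate only if resolution is the target. If Table 2 is what the sponsor means, a true 5-point deficit lies inside the margin and 25% is simply power. This is correct, and it is why the figures are illustrative only. It does not remove the conflict, because the article names resolution as the endpoint twice.

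Finally, the trial is double-blind and stratified by centre, so inconsistent reading between sites should not favour one arm. It would add noise, which can itself blur a real difference.

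**Conclusion.** The point holds as a contradiction in the definition of the primary endpoint. It changes who counts as cured, and the direction of the resulting dilution favours non-inferiority. That direction rests on reading initial as at presentation and on the switch criteria in the Inclusion criteria. The size cannot be derived from the documents. The rise from about 3% to about 25% depends on assumed resolution of 85% v 75%, on half of unresolved patients counting as reduced, on that share being equal in both arms, and on resolution being the intended target. The sample size should not be called wrong: 109 per arm is correct at 92.5%, and the power falls short only if that rate does not describe the endpoint actually used.

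**What to change.** Use one definition throughout, settled before the 100-participant interim look and before unblinding. Change the Table 2 row to: alive, with resolution of all initial local and systemic FUTI-related symptoms (return to the pre-infection level for pre-existing symptoms such as incontinence), and without additional systemic antibiotic therapy for UTI. Report reduction only as a secondary category. An explicit threshold for reduction would also end the ambiguity, but the abstract and Endpoints text would then have to change; aligning the table with the endpoint already stated twice is the smaller step.

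State that the 92.5% rate and the 10-point margin refer to the chosen definition. If the expected resolution rate is lower, restate the power from the table in the working.

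The cost is a change of wording and of the endpoint derivation. Table 1 lists a patient questionnaire before randomisation and at both follow-ups, so no extra visit appears necessary, but its content is not described. The sponsor should confirm that it records residual symptoms and their pre-infection level. Observed cure rates may be lower and the stated power less favourable; restoring 80% power at 85% resolution would need 201 evaluable patients per arm.

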#### Intention to treat and per-protocol analysis

Participants are evaluable if they are randomized and received at least one dose of the study drug, and all will be included in the intention to treat analysis. Analysis of all endpoints will be performed according to the intention-to-treat principle, on which data non-inferiority is based. A per-protocol analysis will be performed for the primary endpoint and the secondary endpoint ‘microbiological cure’ for patients that completed at least 80% of study medicines.

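### Clinical cure counts only antibiotics given for UTI, and the stated per-protocol criterion keeps women given another E. coli-active drug, so neither analysis would detect a failure masked that way

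*Protocol article*

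**What the plan says.** All places are in the protocol article.

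- **Endpoints, Table 2, clinical cure.** The definition has two parts. The first is "Alive with reduction of all initial local and systemic FUTI related symptoms". The second is "without additional systemic antibiotic therapy for UTI (except antibiotic prophylaxis"). The primary assessment is at 6–10 days after the end of treatment.
- **Endpoints, Table 2, additional antibiotic use.** This secondary endpoint has the same limit by indication: "additional systemic antibiotic therapy for UTI (except antibiotic prophylaxis"). It would not pick up antibiotics given for other reasons either.
- **Exclusion criteria.** "concomitant systemic antibacterial treatment" is an exclusion at entry. No reason is given, and the article states no rule for such treatment started after randomization.
- **Intention to treat and per-protocol analysis.** "Analysis of all endpoints will be performed according to the intention-to-treat principle, on which data non-inferiority is based". The per-protocol analysis covers the primary endpoint and microbiological cure, "for patients that completed at least 80% of study medicines". Non-study antibiotics are not mentioned there.

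**The concern.** A systemic antibacterial prescribed between randomization and the 6–10 day visit for, say, pneumonia or a skin infection may also be active against the E. coli that caused the UTI. It may then suppress a failure of the study drug. Under Table 2 the prescription does not count against cure, so the woman is scored on survival and symptom reduction. She also stays in the per-protocol set if she took 80% of her study medicines.

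In a non-inferiority trial the direction matters. If the same share of failures is masked in both arms, the arm with more failures loses more of them. The observed difference shrinks, and a drug that is truly worse by the margin is more likely to pass. The per-protocol analysis is where one would look for protection against this, and its stated criterion does not provide it.

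**Working it through.** **Inputs from the Sample size calculation section:** "assumed cure rate of 92.5% for both groups", margin 10 percentage points, two-sided alpha 0.05, power 80%, 109 evaluable women per arm.

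**Assumption:** a share u of would-be failures is turned into cures by a non-study antibiotic. The documents give no figure for u, so a range is shown.

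**1. The plan's own figure.** With the unpooled normal approximation,

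n = 2 × 0.925 × 0.075 × (1.960 + 0.842)² / 0.10² = 108.9, so 109 per arm.

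This reproduces the stated number. The point raised here does not affect it.

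**2. Masking at the margin.** Suppose ciprofloxacin truly cures 92.5% and fosfomycin 82.5%, so the failure rates are 7.5% and 17.5%. With equal masking in both arms the observed difference is

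(0.175 − 0.075) × (1 − u) = 0.10 × (1 − u),

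that is, 9.5 points at u = 5% and 9.0 points at u = 10%.

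**3. Chance of wrongly declaring non-inferiority.** All binomial outcomes with 109 per arm were enumerated. Non-inferiority was declared when the unpooled two-sided 95% interval for the difference excluded 10 points.

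| Share of failures masked (u) | Both arms | Fosfomycin arm only |
|---|---|---|
| 0% | 2.98% | 2.98% |
| 5% | 3.88% | 4.60% |
| 10% | 5.05% | 6.93% |
| 20% | 8.50% | 14.6% |

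The value at u = 0 is above the nominal 2.5% because the unpooled interval is approximate at this sample size. That excess has nothing to do with masking. The increments due to masking in both arms are 3.88 − 2.98 = 0.9 points at u = 5% and 5.05 − 2.98 = 2.1 points at u = 10%. A normal approximation starts from 2.5% and gives 3.3% and 4.2%. Relative to its own baseline, each method shows about a 1.7-fold rise at u = 10%.

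**4. In women.** Expected failures per 109 are 0.175 × 109 = 19.1 on fosfomycin and 0.075 × 109 = 8.2 on ciprofloxacin. Masking of 5% is therefore about 1.0 and 0.4 women.

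**5. What it costs to count every such woman as non-cure.** Let q be the share of otherwise cured women who receive such an antibiotic, equal in both arms (again an assumption). Cure rates become 0.925(1 − q) and, at the margin, 0.825(1 − q). The same enumeration gives:

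| q | True margin difference appears as | One-sided error | Power at equal cure rates |
|---|---|---|---|
| 5% | 9.5 points | 3.4% | 63% |
| 10% | 9.0 points | 4.0% | 51% |

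Counting these women as failures thus also dilutes a true difference, and it loses power as well.

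**The case against.** The case for leaving the plan alone has several parts.

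- **Limiting failure to UTI-directed antibiotics is defensible.** Counting any antibiotic as failure adds events unrelated to the study drug, dilutes a true difference and costs power. This stands, and it is why the primary definition should not change.
- **The article is a condensed text.** The full protocol, case report form or analysis plan may already capture all antibiotics and list prohibited-medication deviations. This stands in part: nothing can be said about what those documents hold. But the article does state the endpoint definition and a per-protocol criterion, and the point concerns what follows from them as written.
- **The size is assumed.** This stands. Step 3 also equates masking with actual rescue. If 5% received such a drug and only half of them were rescued, u is 2.5% and the error is 3.4%.
- **Other safeguards exist.** Double-blind, double-dummy treatment limits differential labelling of the indication, so the column for the fosfomycin arm alone is the less likely scenario. It does not prevent equal masking in both arms. All-cause readmission, ICU admission and mortality do not depend on the indication, but they do not identify a suppressed symptomatic failure. Nor does microbiological cure, since a drug active against the isolate may clear the urine too.

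A reader might also infer more than the text supports:

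- **That such a woman is automatically a cure.** She is not: she must be alive with all initial symptoms reduced.
- **That the plan adopts a protection at entry and then abandons it.** The exclusion criterion carries no stated rationale, so no such contradiction can be shown.
- **That recurrences in bacteraemic women admitted without local symptoms would be treated under another label.** Those women enter because UTI is the presumed source, and nothing in the article suggests later relabelling.

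**Conclusion.** The gap is real and modest. Followed as written, neither the intention-to-treat analysis nor the per-protocol analysis can detect a failure suppressed by an E. coli-active antibiotic given for another indication, and any such masking favours non-inferiority. The documents do not show that failures will be hidden; it is a risk of unknown frequency. If 5% or 10% of would-be failures were masked equally in both arms, the one-sided error at the margin would rise from 2.98% to 3.9% or 5.0%, with 5% amounting to about one fosfomycin failure per 109. These figures rest on the assumed masking shares, true cure rates of 92.5% and 82.5%, and an unpooled 95% interval. The sample size and the primary endpoint rule are not called into question. This is a cheap improvement that should be made, not a flaw that invalidates the design.

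**What to change.** Keep the primary intention-to-treat definition of clinical cure. Then:

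1. Record every systemic antibacterial, with dates and indication, from randomization to each follow-up visit, if this is not already done.
2. Before unblinding, classify each one for in vitro activity against the woman's baseline isolate. The Data collection section says that isolates are stored for further susceptibility testing, so this should be feasible.
3. Exclude from the per-protocol set any woman who received an active non-study agent before the 6–10 day assessment, unless she is already scored non-cure.
4. Add one pre-specified intention-to-treat sensitivity analysis that counts these women as non-cure, labelled as supportive.

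The cost is a case report form entry, a blinded classification, one extra analysis and a slightly smaller per-protocol set. The sensitivity analysis adds failures unrelated to the study drug and loses power, as step 5 of the working shows. It should be read beside the primary and per-protocol results and not replace either.
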